### Randomisation and blinding

Following fully signed local authority (and service provider if applicable) and centre agreements, participating centres within each local authority will be randomised to HENRY or control in a 1:1 allocation ratio by the Leeds Clinical Trials Research Unit. Minimisation, incorporating a random element, will be used to ensure the treatment groups are well balanced for the following characteristics:

Size of centre (≤8/>8 permanent centre members of staff, not including staff using the centre such as Health Visitors, nursery workers, etc).Area-level ethnicity (<80%/≥80% white British using Census data based on centre postcode).Area-level deprivation (≤10%/>10% ranking within Index of Multiple Deprivation at the lower layer super output area).

Parents and centre staff will not be blinded due to the nature of the intervention. Data collection staff will be blinded to centre allocation (and thus the participants’ treatment arm).

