**Figure 2 F2:**
[figure not shown]
Flow of recruitment. CRN, Clinical Research Networks; CTRU, Clinical Trials Research Unit; HENRY, Health, Exercise and Nutrition for the Really Young.

Local authorities will be asked to nominate approximately twice the number of centres for which they wish to commission HENRY, so that approximately half can be randomised to receive HENRY and half can be randomised to control. Although there are no exclusions based on the demographics of centres, location will be monitored and commissioners encouraged to nominate centres to include a range of diverse social and environmental characteristics. Centre managers will be given information about the research and asked to provide consent for their centre to participate through a collaboration agreement.

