### Sample size

41 centres per arm (from 10 to 14 local authorities), each recruiting 12 parents on average (4 parents from 3 programmes, 984 parents in total) will provide 90% power to detect a small standardised effect size of 0.27 as per previous trials (25–28) for BMI z-score at a 5% significance level, assuming an ICC of 0.03 (16, 25, 29–31) to account for clustering by centre, a coefficient of variation of 0.48 to account for variation in centre recruitment and 20% loss to follow-up.^18^

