### Data analysis plan

Analysis will be carried out on the intention-to-treat (ITT) population defined as all local authorities/centres randomised and all parents registered to the trial, regardless of adherence to the protocol, withdrawal of consent or losses to follow-up. A two-sided 5% significance level will be used for statistical endpoint comparisons. No interim analyses are planned, except for safety data that are required for review by the data monitoring and ethics committee.

The flow of local authorities, centres and participants through the trial will be presented in a Consolidated Standards of Reporting Trials diagram.

The primary outcome, child age-adjusted and sex-adjusted BMI (BMI z-score) will be analysed using a multilevel linear regression with children nested within centres and centres treated as a random effect. The model will be adjusted for the following fixed effects: centre-level stratification factors, important parent-level and child-level covariates (eg, baseline child BMI z-score and sex, parent BMI), and other relevant known predictors of outcome. Missing data will be imputed at the individual participant level where appropriate. Estimated mean differences will be reported with 95% confidence intervals, p values and ICCs. Model diagnostics will be used to check the underlying assumptions of the model and alternative methodology will be used if required.

Sensitivity analyses of the primary endpoint will be conducted to assess the impact of missing data, the choice of imputation model and the missing at random assumption, as appropriate. If contamination between intervention and control centres is identified, a sensitivity analysis excluding the relevant control centres will be conducted.

If numbers allow, exploratory subgroup analysis will examine differences in intervention effect between different socioeconomic and ethnic groups, and also between online and face-to-face delivery of HENRY.

For secondary outcomes, summary statistics will be presented at baseline and 12 months post parent registration overall and by arm (means, SD, medians, minimum, maximum and quartiles for continuous variables, and counts and percentages for categorical variables).

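### Centres are randomised 1:1 within local authority, but authority is not named as a balancing factor or in the primary model; if authorities differ, the test may be mildly conservative

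*Protocol article*

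**What the plan says.** **Allocation.** Under Randomisation and blinding, "participating centres within each local authority will be randomised to HENRY or control in a 1:1 allocation ratio". The recruitment text after Figure 2 agrees: each authority nominates about twice as many centres as it wishes to commission, "so that approximately half can be randomised to receive HENRY and half can be randomised to control". An authority may enter with as few as two centres, ideally six or more.

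**Balancing factors.** The same section continues: "Minimisation, incorporating a random element, will be used to ensure the treatment groups are well balanced for the following characteristics". Three follow: centre size, area-level ethnicity and area-level deprivation. Local authority is not listed.

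**Primary model.** The Data analysis plan specifies a "multilevel linear regression with children nested within centres and centres treated as a random effect". On the fixed part: "The model will be adjusted for the following fixed effects: centre-level stratification factors, important parent-level and child-level covariates", with baseline child BMI z-score, child sex and parent BMI as examples, "and other relevant known predictors of outcome". Local authority is named neither as a fixed effect nor as a level. The medium-term analysis is to follow the same approach as the primary outcome.

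**Error rate and size.** "A two-sided 5% significance level will be used for statistical endpoint comparisons". The Sample size section says that 41 centres per arm, from 10 to 14 authorities, "will provide 90% power to detect a small standardised effect size of 0.27 as per previous trials", with clustering by centre only (ICC 0.03).

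**The concern.** When randomisation is restricted within blocks, differences between blocks cancel from the treatment comparison. A model that omits the blocks still counts those differences as noise. Here the block would be the local authority, and the noise would sit in the centre variance.

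The article gives reasons why authorities might differ: each chooses its own delivery model for HENRY, and standard services vary between and within local areas. The intention-to-treat definition also refers to local authorities as randomised units alongside centres, so the authority is recognised as a design level and then does not appear in the model.

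At stake are some precision and agreement between the stated and actual test level. The treatment estimate is not biased by the omission.

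**Working it through.** **Step 1. Reproduce the plan's sample size.** Inputs from the Sample size section: effect 0.27 SD, two-sided alpha 5%, power 90%, 41 centres per arm, 12 parents per centre, ICC 0.03, CV 0.48, 20% loss.

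- Individually randomised size: 289 per arm.
- Analysed per centre: m = 12 × 0.8 = 9.6.
- Design effect: 1 + ((1 + 0.48²) × 9.6 − 1) × 0.03 = 1.324.
- Total: 2 × 289 × 1.324 / 0.8 ≈ 957, within 3% of 984.
- Power at 41 centres per arm: 90.9% (90.2% using t with 80 df).

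The stated figure reproduces. Using the recruited 12 rather than 9.6 in the design effect gives a total of 1021 and power of 89.0%.

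**Step 2. Effect of omitting authority when allocation is balanced within it.** Take total variance 1 and equal centres of 9.6. Let s be the share of the 0.03 ICC that lies between authorities. The article gives no value, so s is an assumption and is varied.

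- Variance of a centre mean as the model sees it: 0.03 + 0.97/9.6 = 0.1310.
- Variance that actually affects the comparison: 0.03(1 − s) + 0.97/9.6.
- SE ratio r = √(first/second). True alpha = 2 × (1 − Φ(1.96 r)).

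| Share s | Second variance | SE ratio | True alpha |
|---|---|---|---|
| 0 | 0.1310 | 1.00 | 5.0% |
| 10% | 0.1280 | 1.012 | 4.7% |
| 25% | 0.1235 | 1.03 | 4.35% |
| 50% | 0.1160 | 1.06 | 3.7% |
| 100% | 0.1010 | 1.14 | 2.6% |

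Two variations on the assumption:

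- With the CV of 0.48 in the design effect, the 50% row becomes √(1.324/1.147) = 1.07.
- If an authority ICC of 0.01 to 0.03 came on top of the centre ICC, the ratio would be 1.04 to 1.11 and alpha 4.2% to 2.9%.

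**Step 3. Power for 0.27 at s = 50%.** The true SE is √(2 × 0.1160/41) = 0.0752, and 0.27/0.0752 = 3.59.

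- Without authority: Φ(3.59 − 1.96 × 1.063) = 93.4%.
- With authority: Φ(3.59 − 1.96) = 94.8%.

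Both exceed 90%, and the gain is 1.4 points. These figures use equal centre sizes and do not charge for degrees of freedom.

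**Step 4. Simulation.** 82 centres, 14 authorities, CV 0.48, REML random-centre model, 3000 runs per setting (Monte Carlo error about 0.4 points on alpha).

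| Allocation | Share s | Alpha, no authority term | Alpha, authority fixed |
|---|---|---|---|
| Within authority | 0 | 5.0% | 4.8% |
| Within authority | 25% | 4.3% | 4.8% |
| Within authority | 50% | 3.6% | 4.8% |
| Within authority | 100% | 3.1% | 4.1% |
| Not restricted | 0 to 100% | 4.5% to 5.3% | 3.7% to 4.8% |

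At s = 50% with restricted allocation, the mean model SE is 0.0810 against an empirical SD of 0.0779, a ratio of 1.04. The direction agrees with Step 2 and the size is slightly smaller.

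**The case against.** **The analysis plan is not shown.** The covariate list is open-ended. A stratum could fall under stratification factors or under other known predictors, and the full analysis plan may already include authority. This limits confidence that the final analysis omits it. It does not remove the point: the article itself fixes the allocation, lists the balancing factors and names the model's levels, and authority appears only in the first of these.

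**The randomisation text may already make authority a stratum.** That is the natural reading, and the commissioning plan supports it. It strengthens the case for naming authority in the model.

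**Baseline adjustment may remove the difference.** Baseline BMI z-score, parent BMI, area ethnicity and deprivation could absorb much of what separates authorities. This stands. Only the residual share counts, and it may be near zero.

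**Stronger readings a reader might infer.**

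- *The test is definitely not at 5%.* This needs both restricted allocation and residual between-authority variance. Without the restriction, simulated alpha stays near 5%.
- *Missing the 5% level means too many false positives.* The error runs the other way.
- *The trial loses precision and also risks putting both centres of a two-centre authority in one arm.* These cannot both apply. The first needs allocation enforced within authority; the second needs it not enforced.
- *The trial is underpowered as a result.* Power without the authority term remains above 90% in Step 3.

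**Conclusion.** The point holds in conditional form. The article describes randomisation within local authority but does not carry authority into the balancing factors or the stated primary model. If the restriction is real and authorities differ after adjustment, the stated analysis is valid but mildly conservative. With an assumed 10% to 50% of the 0.03 ICC between authorities, the SE is about 1% to 6% too large and true alpha is about 4.7% to 3.7%. The extreme case, with all of the ICC between authorities, gives 14% and 2.6%. A zero share gives no effect.

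The direction is secure under those two conditions. The size is not, because the documents supply no between-authority variance. This is a worthwhile correction, not a threat to the trial's validity or its planned power.

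**What to change.** 1. Under Randomisation and blinding, state that local authority is a randomisation stratum, with the three listed characteristics minimised in addition.
2. In the Data analysis plan, add local authority to the primary model: as fixed effects, or as a random level above centre if many authorities contribute only two centres. Do the same in the models that follow the same approach.

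**Cost.** The change is wording only. With 14 authorities, fixed effects use 13 of the 82 − 2 = 80 between-centre degrees of freedom, leaving 67. In the simulation with allocation restricted within authority and no authority variance, the empirical SD rises from 0.0820 to 0.0829, about 1%. At a 50% share, power rises by roughly 1 point.

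**Condition.** The two steps belong together. If allocation is not in fact restricted within authority, fixed authority effects can cost precision: with no authority variance, the simulated SD rises from 0.0811 to 0.0897, about 11%. The allocation statement should therefore be settled first.

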### Active intervention

HENRY was set up with Department of Health funding in 2008 and has been widely commissioned by more than 50 areas (training >15 000 practitioners and providing programmes to ~24 500 parents). It includes core practitioner training and group facilitation training (www.henry.org.uk).^20^

HENRY is delivered primarily within Sure Start centres and other children’s centres, as well as other community settings, including schools, mosques and churches. Local authority areas can choose to have HENRY programmes delivered directly by HENRY central teams (less common approach), pay to commission training, licensing and support from HENRY (most common approach), offer a blended approach or provide training to local staff to deliver programmes (most common in larger local authority areas).

#### Intervention training for practitioners

Core practitioner training supports staff to deliver the HENRY approach, which incorporates evidence-based behaviour change models, including the family partnership model, motivational interviewing and solution-focused support, with information about a healthy start that is consistent with national guidance. This training is designed to allow staff to integrate evidence-based models to develop motivation and support lifestyle change for families. This can then be embedded into all interactions with families, in addition to supporting positive changes to the centre environment (space to play, freely available water, food policies, etc). Training is provided to health visitors, dieticians and staff (eg, at children’s centres, community centres/hubs—hereon called ‘centres’) allowing parental support to be an intrinsic part of their role, while influencing culture and policy within early years settings. Training is designed to consistently influence the environment and practice immediately following training.

Facilitator training is delivered to a (usually) smaller selection of staff who have attended core training to certify them to deliver small group sessions ‘Right from the Start’. This training enables the delivery of an 8-week universal ‘Right from the Start’ programme to parents to provide practical skills in authoritative parenting skills, increasing self-esteem, adopting healthy family lifestyles, goal setting, oral health, active play, portion sizes and learning about food labels.

Training can be delivered in-person or remotely, depending on commissioner and facilitator preference. To allow a richer level of communication, the in-person training can be completed in a shorter time frame (2-day in-person training is delivered over 6 weeks remotely).

#### Programme delivery to parents

The ‘Right from the Start’ programme is delivered to groups of approximately 8–10 parents over 8 sessions. Each interactive session focuses on a separate theme and includes resources for families to take home. Each centre delivers 2–3 ‘Right from the Start’ group programmes per year, each consisting of 8×2 hours sessions.

Programmes can be delivered remotely or face to face. We will include both delivery modes in the proposed research. This will allow us to be flexible depending on external issues, in addition to supporting an evaluation of a pragmatic intervention. Our analysis plan includes consideration of different delivery approaches.

Parents with a child aged up to 5 years are eligible to attend HENRY. The programme can be tailored to specific groups or parents, for example, to align with dietary practices for different ethnicities or religion. Language needs are addressed locally depending on the population needs, with some areas providing dedicated support. Without this, the other approach is to invite parents to attend with a friend or family member to support translation and other activities. Although considered to be a universal programme, practitioners often refer families ‘at risk’ to HENRY and the delivery model within children’s centres allows parents from the most deprived neighbourhoods to attend.

Parents receive a standardised manual as part of the programme. To monitor adherence, session attendance will be recorded for parents who consent.

### Control intervention

Staff within control centres will not receive HENRY training and will continue to deliver usual programmes or ‘standard practice’ (eg, ‘stay and play’, ‘cook and eat’). In short, this means that families registered to take part in the research will receive the standard level of support provided within their community/centres. Services are aimed at supporting families with a focus on the most disadvantaged families. These vary between and within local areas but usually include access to health visiting teams, breastfeeding support, parenting advice and access to specialist services including speech and language therapy.

### Outcomes

The primary outcome for the trial is child age-adjusted and sex-adjusted BMI z-score assessed at 12 months post parent registration.

Secondary outcomes will be assessed at the same time point (defined short term), after 3 years (medium term) and will be forecasted across the life course (longer term). Individual-level outcomes are summarised in table 1 (see online supplemental table 1) for a full list of outcomes and measures).

10.1136/bmjopen-2023-081861.supp1Supplementary data

**Table 1 T1:** Outcome data collection summary (see online supplemental table 1) for a full list of data and outcomes

Outcomes	Measures	Collected by	Participant/staff baseline	Short-term follow-up (12 months postregistration)	Medium-term follow-up (3 years)*	Longer-term follow-up†
Child age-adjusted and sex-adjusted BMI Z-score, child height, child weight, unadjusted BMI and weight/BMI percentiles	Measured	LCRN‡ (baseline and 12 months follow-up) Longer term: CTRU accessing routine data	x	x	x	
Sibling age-adjusted and sex-adjusted BMI, height (m), weight (kg), unadjusted BMI and weight/BMI percentiles		CTRU accessing routine data			x	
Parent self-efficacy	Dumka^27^	LCRN	x	x		
Family eating/activities	Golan^28^	LCRN	x	x		
Feeding questionnaire	Baughcum^29^	LCRN	x	x		
Dental health (child)	Dental questionnaire	LCRN	x	x		
Parent height and weight:	Measured	LCRN	x	x		
Parent waist circumference	Measured	LCRN	x	x		
Staff:						
Staff screening	Staff screening form	Staff self-complete at centre				
Staff height and weight	Measured	Self-measure	x	x		
Staff waist circumference	Measured	Self-measure	X	x		
Routine data:						
NCMP Child and sibling data (trial participants)		CTRU			x	
NCMP regional child data (not trial participants)		CTRU			x	

*Medium-term outcomes will be gathered from routinely collected data (from health visitors and/or the NCMP).

†Longer-term outcomes will be based on matched cohorts of (Millennium Cohort Study).^21^

‡Local Clinical Research Network (England only). Other devolved nations will train researchers/equivalent staff to collect data.

BMI, body mass index; CTRU, Clinical Trials Research Unit; LCRN, local clinical research network; NCMP, National Child Measurement Programme.

### Data collection

Table 1 provides information about the types of data collected and how these are collected. Baseline and follow-up data (12 months) will be collected within participant homes by trained LCRN staff (or equivalent trained staff in the devolved nations). Where preferred by the participant, there will be options to collect data in the children’s centre. The majority of questionnaires completed during home visits will be interviewer administered. Centre-level outcomes will be completed by a nominated member of centre staff (usually the centre manager or HENRY facilitator). Staff-level data will be self-completed and entered directly on to the online database.

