#### Secondary objectives of randomised controlled trial

To determine whether HENRY improves parent self-efficacy, eating behaviours, feeding behaviours, dental health and quality of life.To explore whether HENRY influences rates of obesity in parents, siblings and staff (health practitioners).To examine the social and physical environment in the children’s centres.To monitor any safety issues from the intervention, including adverse events or unintended consequences

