### Eligibility criteria

Local authorities can be new to HENRY or already commissioning HENRY, provided they have at least two centres (ideally six) meeting centre eligibility criteria. Local authorities using external teams outside of the centre to deliver HENRY programmes (eg, health visitors) will be eligible, in addition to those wishing to train internal centre staff to deliver programmes (the most common model). Local authorities without coverage of a NIHR local CRN (LCRN; the teams responsible for collecting trial data from parents and staff) will not be eligible.

Centres: Any type of centre or other early years setting such as a nursery or community venue will be eligible to take part provided that they do not already deliver HENRY, and their staff have not received HENRY training (within the past 2 years). This includes both public and private nurseries. Centres where staff are shared between nominated centres will not be eligible. Centres must aim to run HENRY programmes starting within 12 weeks of training completion and plan to run three programmes during their trial participation period (approximately 18 months). They should be in geographically separate areas to protect against contamination (judged on a case by case basis) and managers must agree to support participant recruitment within their centres. If the centre operates as part of a cluster, that cluster must be deemed to be HENRY naive. HENRY naive clusters are defined as a group of centres within a cluster that does not include any centres that are (a) currently delivering HENRY or (b) have been trained to, or delivered HENRY within the past 2 years.

Centres that are either currently delivering HENRY or have previously delivered HENRY in the last 2 years are not eligible.

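### Centre-level outcomes may be completed by the HENRY facilitator, a role only intervention centres can have, so the respondent's role can differ by arm

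*Protocol article*

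**What the plan says.** Under Data collection, the protocol article says: "Centre-level outcomes will be completed by a nominated member of centre staff (usually the centre manager or HENRY facilitator"). The rule is the same for every centre.

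Four other sections bear on who that person can be:

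- Intervention training for practitioners: "Facilitator training is delivered to a (usually) smaller selection of staff who have attended core training". The same section says that core training supports improvements in the centre itself, such as room for play, access to water and food policy.
- Control intervention: "Staff within control centres will not receive HENRY training and will continue to deliver usual programmes".
- Eligibility criteria: a centre may enter only if it does not already deliver HENRY and "their staff have not received HENRY training (within the past 2 years").
- Randomisation and blinding: "Parents and centre staff will not be blinded due to the nature of the intervention".

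The outcome at issue serves one of the secondary objectives, which begins "To examine the social and physical environment in the" and refers to the participating children's centres. For secondary outcomes, the Data analysis plan describes summary statistics at baseline and 12 months, overall and by arm.

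**The concern.** A between-arm comparison assumes that the outcome is obtained in the same way in both arms. Here the permitted respondent depends on allocation. In a control centre it must be the manager or another person with no HENRY role. In an intervention centre it may be the person trained to deliver HENRY, who would be describing the surroundings that the training aims to improve. If facilitators and managers would describe the same centre differently, that difference appears in the by-arm summary as though it were an effect of HENRY.

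This is separate from the general lack of blinding. Centre staff cannot be kept unaware of allocation in an open trial of this kind, but a respondent role that varies with allocation can be avoided. The blinded data collectors, who measure the children and parents, do not complete the centre-level outcomes, so their blinding gives no protection here.

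**Working it through.** The plan gives no figure for the centre-level outcomes, so there is none to reproduce. The sample-size calculation concerns child BMI z-score, and nothing in it depends on who completes the centre form. The check is a comparison of sections.

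1. **Who may respond.** Data collection names two usual respondents, the manager and the HENRY facilitator, with no distinction by arm.
2. **How a facilitator comes to exist.** By facilitator training, taken after core training (Intervention training for practitioners).
3. **Whether a control centre can have one.** Control staff receive no HENRY training during the trial (Control intervention). Centres that deliver HENRY, or whose staff were trained within the past 2 years, are excluded at entry (Eligibility criteria). Someone trained longer ago could in principle work in a control centre, but would not be acting there as a HENRY facilitator, because control centres keep to their usual programmes.
4. **Whether an intervention centre always has one among its staff.** No. "Local authorities using external teams outside of the centre to deliver HENRY programmes (eg, health visitors) will be eligible". Where delivery is external, the facilitator may not be a member of centre staff, and the manager is then the likely respondent. Training internal staff is, however, described as the most common model.
5. **Result.** The facilitator option is open in many intervention centres and in no control centre.

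The consequence can be written as an expression. Let p be the share of intervention centres in which the facilitator responds. Let δ be the average difference between a facilitator's and a manager's answers about the same centre. If managers or similar staff respond everywhere else, then

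bias in the by-arm difference = p × δ.

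This is zero if p = 0 (managers always respond) or δ = 0 (the items leave no room for judgement). The document gives neither p nor δ, and does not fix the sign of δ. A number put on the product would come entirely from assumption, so none is given here.

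**The case against.** The strongest reply is that the wording permits the difference but does not require it. The manager is named first and exists in both arms. If managers complete every form, the role does not differ. This stands, and it is why the point is put as a risk.

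A second reply is that the instrument is not shown. Table 1 covers individual-level outcomes, and the full list of measures is in a supplement. Items such as whether water is available or a food policy exists may be recorded as facts and would leave less room for the respondent's view. This also stands. It limits the likely size, but it does not make the rule sound.

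A third reply is that the article condenses a fuller protocol, so operational detail may be found there. That is fair for recording the respondent's role or keeping the same person over time, whose absence from the article is no fault. It does not answer the main point, because the respondent rule is stated in the article and is itself unequal between arms.

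A fourth reply is that the fix achieves little, since all centre staff are unblinded and an intervention-arm manager may have had core training too. This is partly right. The fix removes the difference in role and leaves knowledge of allocation in place.

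A reader might also make two stronger inferences that the document does not support. One is that the respondent changes from manager before training to facilitator afterwards, so that change within a centre is distorted. The Data collection section gives neither the timing of centre-level measurement nor any switch of respondent, and one nominated person responding throughout fits the text equally well. The other is that a bias of a particular size has been shown. As set out above, it cannot be calculated.

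**Conclusion.** The point holds as a minor one. The stated rule lets the respondent's role depend on allocation, because a HENRY facilitator can be found only in intervention centres. This may bias the by-arm description of the centre environment, which HENRY training is meant to change.

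The conclusion rests on two readings of the text: that the facilitator role arises only through HENRY training, and that the same respondent rule covers both arms. The size and direction of any bias are unknown.

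The consequence is confined to the interpretation of centre-level outcomes under one secondary objective, for which the article states summaries by arm and no formal test. A by-arm summary still invites comparison, so descriptive reporting reduces the weight of the problem without removing it. The primary outcome is measured by blinded local research network staff and is not affected, nor is any sample-size or power figure.

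**What to change.** In the Data collection section, remove the HENRY facilitator as a respondent for centre-level outcomes. Name one role that exists in both arms, such as the centre manager or a deputy with no part in delivering HENRY. Use the same role at each time point and record the respondent's role on the form.

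If forms have already been completed, tabulate the respondent's role by arm alongside the centre-level results and state the limitation in the report.

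The cost is a wording change and one extra item on the form. It needs no additional staff and does not alter the sample size. The downside is slightly more work for managers in centres where the facilitator would otherwise have responded. Because the change leaves the respondent unblinded, and intervention-arm managers may have had core HENRY training, the report should still describe these outcomes as unblinded staff reports.
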